## Abstract

**Background:**

Chronic migraine is a chronic medical condition associated with resistance to pharmacological treatment and poor benefits from the psychological interventions studied to date, including acceptance and commitment therapy or mindfulness. This manuscript describes the rationale and methods for a pilot feasibility study designed to (1) establish and (2) evaluate the feasibility and acceptability of research procedures and interventions to investigate whether well-being therapy improves outcomes relative to a control condition.

**Methods:**

The current intervention will use a randomized controlled trial design, wherein 30 outpatients with chronic migraine will be randomized (1:1) to well-being therapy (*n* = 15) or to a control condition (*n* = 15). Primary outcomes include the level of disability caused by migraine and the frequency, duration, and intensity of migraine attacks; the secondary outcomes focus on anxiety, depression, psychological well-being, euthymia, and distress. Primary and secondary outcomes will be assessed at baseline, after sessions 4 and 8, and at 3-month follow-up. The Ethical Review Boards at the University-Hospital Careggi has approved the study (5th December 2017).

**Discussion:**

Identifying medium-term interventions able to improve chronic migraine is relevant to manage this illness. The present randomized trial might represent a step forward for managing chronic migraine by means of psychological interventions.

**Trial registration:**

ClinicalTrial.gov Identifier: NCT03404336. Registered on 19 January 2018.

**Electronic supplementary material:**

The online version of this article (10.1186/s13063-018-2944-5) contains supplementary material, which is available to authorized users.

## Background

Migraine is a prevalent disabling condition affecting approximately 15% of subjects in the general population [1]. Migraine can be episodic (i.e., less than 15 headache days per month) or chronic (15 or more headache days per month for at least 3 months) [2–5], the latter affecting 1–3% of the general population [6]. Chronic migraine is the most disabling form of migraine, resulting in lower socioeconomic status and health-related quality of life as well as increased headache-related burden [6]. Chronic migraine is often resistant to treatment [7] and the efficacy of stress-oriented psychotherapeutic interventions, such as acceptance and commitment therapy and mindfulness, has been shown to be poor [8–18].

Well-being therapy (WBT) is a short-term (i.e., 8 sessions) well-being-oriented psychotherapeutic strategy emphasizing self-observation of patient’s well-being with the use of a structured diary, interaction between patients and therapists, and homework [19–21]. It is based on the model of psychological well-being developed by Jahoda in 1958 [22] and further refined by Ryff [23]. The goals of WBT are the improvement of the psychological well-being and the achievement of a state of euthymia [19–21]. In previous randomized controlled trials, WBT was found to be efficacious in reducing relapse rates in depressed adults [24, 25] and in treating generalized anxiety disorder [26] and cyclothymia [27], suggesting that psychological well-being may be increased by a specific psychotherapeutic method and that such increase may yield a protective and preventive effect. WBT was also shown to be efficacious when distress-oriented psychotherapeutic interventions did not produce benefits [28].

We designed a pilot study to (1) establish and (2) evaluate the feasibility and acceptability of research procedures and interventions to investigate whether WBT improves outcomes relative to a control condition in chronic migraine patients who were resistant to pharmacological treatment. Although WBT might be a complementary therapeutic option [29], no studies have addressed the potential of such psychological intervention for chronic migraine. The present manuscript describes the study design and procedures for a pilot randomized controlled trial investigating feasibility, acceptability, and effects of WBT in chronic migraine patients.

## Methods

This protocol is reported in accordance to the Standard Protocol Items: Recommendation for Intervention (SPIRIT) guidelines [30, 31]. For the SPIRIT Checklist, see Additional file 1.

### Study overview

This is a 16-week, stage 1b, single site study designed to evaluate the feasibility, acceptability, and preliminary effects of two psychological interventions in chronic migraine patients. It was designed to evaluate the feasibility of conducting a two-arm pilot randomized controlled trial with participants randomized (1:1) to WBT or to a control condition. Primary and secondary outcomes will be assessed at baseline, after sessions 4 and 8, and at 3-month follow-up. Figure 1 provides an overview of the study design and timeline.

**Fig. 1 Fig1:**
[figure not shown]
Summary of study timeline. *PT* post treatment assessment, *3 M* 3-month follow-up

### Specific aims

The specific aims and hypotheses for this pilot trial are (1) to examine, from baseline to 3 month follow-up, the level of disability due to migraine and the frequency, duration, and intensity of migraine attacks. We hypothesize that patients receiving WBT will show a better outcome compared to those assigned to the control condition (primary outcome); and (2) to examine, from baseline to 3 month follow-up, the level of anxiety, depression, psychological well-being, euthymia, and distress. We hypothesize that patients receiving WBT will show lower anxiety, depression, and distress, and greater psychological well-being compared to those assigned to the control condition (secondary outcome).

### Participant selection recruitment and retention

Eligibility criteria for this ongoing pilot trial (target *n* = 30) include (1) 18–65 years of age; (2) Italian mother tongue; (3) a diagnosis of chronic migraine according to the International Classification of Headache Disorders [2], thus presenting specific features (i.e., unilateral and pulsating pain of moderate or severe intensity, which is aggravated or precipitated by routine physical activities and is combined with nausea and/or vomiting, photophobia, and phonophobia) and migraine headache on 15 or more days per month; (4) headache chronicity for a minimum of 1 year and pattern of headache symptoms stable for a period of at least 6 months [32]; (5) no pharmacological therapy or dietary supplement use for chronic migraine or pharmacological therapy/dietary supplement use for chronic migraine stable for at least 3 months; and (6) psychotropic medication allowed only if stable for at least 3 months.

Exclusion criteria are (1) a diagnosis of headaches due to medication overuse; (2) co-occurrence of psychiatric disorder(s) according to the Diagnostic and Statistical Manual of mental disorders 5th edition (DSM-5) [33], as diagnosed via the MINI International Neuropsychiatric Interview [34]; (3) co-occurrence of chronic unstable medical conditions [32]; (4) being pregnant or lactating [32]; (5) under exogeneous hormone treatment (i.e., hormonal contraceptives, postmenopausal hormone therapy) [32]; or (6) any other condition that, according to the investigators’ opinion, may alter the ability of the patient to follow study procedures.

Participants will be recruited from the SOD Headache Centre and Pharmacologic Clinic of the Careggi University Hospital of Florence. Research assistants (RAs) will screen participants for preliminary eligibility and those who meet initial eligibility criteria will be asked to attend the clinic for an in-person evaluation where informed consent is obtained. The current study employs several measures to minimize attrition. All participants will be assessed by clinical psychologists who will collect sociodemographic and clinical data.

### Randomization

Following eligibility determination, participants will be randomly assigned to either WBT or a control condition. Block randomization of size two will be used. The two groups will be balanced for age, sex, education, and headache severity. The allocation schedule has been created by the principal investigator (FC) using a computerized random number generator and is concealed to the investigators responsible for enrollment. When a registered patient is randomized, the investigator will contact the principal investigator who will communicate the assigned treatment group. Single blindness will be ensured.

#### Study interventions

Figure 2 provides an overview of the study procedure.

**Fig. 2 Fig2:**
[figure not shown]
Two-arm randomized controlled trial design and data collection schedule

### Well-being therapy (WBT)

WBT is used as the only non-pharmacological therapeutic strategy. Eight sessions (Table 1) will be delivered every other week, with a duration of 60 min each. The manualized WBT will be used [19–21]. The initial phase is concerned with self-observation of psychological well-being. Once the instance of well-being is properly recognized, the patient is encouraged to identify thoughts, beliefs, and behaviors leading to premature interruption of well-being (intermediate phase). The final part involves cognitive restructuring of dysfunctional dimensions of psychological well-being and meeting the challenge that optimal experiences may entail [19–21]. An assessment of treatment adherence, satisfaction, and side effects will be performed via ad hoc questions.

**Table 1 Tab1:** Well-being therapy (WBT) sessions according to Fava [19, 21] and Fava et al. [20]

Session	Focus	Objectives	Tool
Session 1	Identifying and setting episodes of well-being into situational context	Report the circumstances surrounding the episodes of well-being rated on a scale of 0 to 100, with zero being absence of well-being and 100 being the most intense well-being	Diary
Session 2	Optimal experiences	Define optimal experiences and report on them	Diary
Session 3	Identifying interfering thoughts and behaviors	Report the thoughts and behaviors that interrupt well-being	Diary
Session 4	Illustrating autonomy	Proposing the dimension of autonomy as material for reflections to the well-being diary	Examples, metaphors
	Reflecting and practicing autonomy	Attempting to explain the premature interruption of well-being with the help of the dimension of autonomy	Daily exposure to pleasurable activities and diary
Session 5	Illustrating environmental mastery	Proposing the dimension of environmental mastery as material for reflections to the well-being diary	Examples, metaphors
	Reflecting and practicing environmental mastery	Attempting to explain the premature interruption of well-being with the help of the dimension of environmental mastery	Daily exposure to pleasurable activities and diary
Session 6	Illustrating positive relations with others	Proposing the dimension of satisfactory interactions as material for reflections to the well-being diary	Examples, metaphors
	Reflecting and practicing positive relations with others	Attempting to explain the premature interruption of well-being with the help of the dimension of satisfactory interactions	Daily exposure to pleasurable activities and diary
	Illustrating personal growth	Proposing the dimension of individual’s style and degree of growth as material for reflections to the well-being diary	Examples, metaphors
	Reflecting and practicing personal growth	Attempting to explain the premature interruption of well-being with the help of the dimension of individual’s style and degree of growth	Daily exposure to pleasurable activities + diary
Session 7	Illustrating self-acceptance	Proposing the dimension of development or self-actualization as material for reflections to the well-being diary	Examples, metaphors
	Reflecting and practicing self-acceptance	Attempting to explain the premature interruption of well-being with the help of the dimension of development or self-actualization	Daily exposure to pleasurable activities and diary
	Illustrating purpose in life	Proposing the dimension of an individual’s balance and integration of psychic forces as material for reflections to the well-being diary	Examples, metaphors
	Reflecting and practicing purpose in life	Attempting to explain the premature interruption of well-being with the help of the dimension of an individual’s balance and integration of psychic forces	Daily exposure to pleasurable activities and diary
Session 8	Placing the experience of WBT in the treatment history of the patient Ending treatment therapy	Review the patient’s effort to contrast interruptions of well-being Continuing cognitive restructuring and in vivo contrast of automatic thoughts Checking the patient’s feeling about ending the therapy	Diary

### Control condition

The control condition will include 8 bi-weekly sessions based on the Lifestyle and Well-being National Institute for Health and Care Excellence (NICE) guidelines (https://www.nice.org.uk/guidance/lifestyle-and-wellbeing) and on the World Health Organization 12 Steps to Healthy Eating (http://www.euro.who.int/en/health-topics/disease-prevention/nutrition/a-healthy-lifestyle). These sessions (Table 2) will inform participants about well-being and the lifestyles that can influence it. No access to specific WBT ingredients will be allowed. An assessment of treatment adherence, satisfaction, and side effects will be performed via ad hoc questions.

**Table 2 Tab2:** Control condition according to the NICE guidelines [34] and World Health Organization-12 Steps to Healthy Eating (http://www.euro.who.int/en/health-topics/disease-prevention/nutrition/a-healthy-lifestyle)

Sessions	Focus
Session 1	Illustrating the concept of lifestyle and well-being
Session 2	Illustrating healthy eating and steps to healthy eating
Session 3	
Session 4	Illustrating physical exercise and how it promotes health
Session 5	Illustrating smoking and tobacco and how they can damage health
Session 6	Illustrating alcohol and how it can damage health
Session 7	Illustrating drug misuse and how it can damage health
Session 8	Illustrating sexual health

#### Monitoring

The subjects will fill in the headache self-report daily diary from 2 weeks before the first session of therapy. Thereafter, they will receive the WBT or the control intervention. The subjects will be re-assessed at the end of session 4 of treatment, at the end of session 8 of treatment, and at 3-month follow-up. Since participants will not be informed if they receive WBT or the control condition, an assessment of treatment credibility will be provided at the end of session 8. At the conclusion of the study, participants will be debriefed and informed that the control condition was necessary to test the study hypothesis.

#### Assessments

Measures selected in this study mirror those commonly used in treatment outcome trials for chronic migraine [9, 13, 15, 16] and are consistent with the international expert consensus guidelines for determining treatment response [35, 36]. These measures include those for screening and eligibility, assessing feasibility, acceptability and patient satisfaction, monitoring patient safety, and determining primary and secondary clinical outcomes. Unless otherwise specified, all measures, including primary and secondary outcome measures, will be administered and collected by Ph.D. level independent evaluators (IEs) naive to study condition.

### Eligibility determination and diagnostic assessment

The diagnosis of chronic migraine will be assessed for the determination of eligibility by the clinical interview according to the International Classification of Headache Disorders [2]. Information on psychological and pharmacological treatment history and co-occurrence of chronic unstable medical conditions will be collected via ad hoc questions previously used [37]. The co-occurrence of psychiatric disorders will be assessed via the MINI International Neuropsychiatric Interview [34], a short structured diagnostic interview validated against the Structured Clinical Interview for DSM diagnoses and against the Composite International Diagnostic Interview for ICD diagnoses as well as against expert opinion in a large sample in four European countries (France, United Kingdom, Italy, and Spain). We will use the Italian version 7.0.0, which allows diagnosis formulation according to the DSM-5 [33].

### Migraine and headache assessment

The level of pain and disability caused by migraines in the patient’s life will be measured using the Migraine Disability Assessment Score questionnaire [38, 39], a 5-item self-administered questionnaire evaluating the influence of migraine on three domains of activity, namely paid work or school, household work, and family, social or leisure activities, over the preceding 3 months; higher scores indicate more severe disability. The Migraine Disability Assessment Score questionnaire showed good internal consistency and high reliability [39]. The level of headache experienced will be assessed via a daily self-report headache diary built according to the guidelines provided by Penzien et al. [32] for trials of behavioral treatments for headache and according to the guidelines provided by Tfelt-Hansen et al. [36] for controlled trials of drugs in migraine treatment. The diary collects information on headache frequency, average headache severity (0 = no headache, 1 = mild headache, 2 = moderate headache, 3 = severe headache), duration of peak headache in hours (start time, end time), intake of symptomatic headache treatments (dose), headache relief after 2 h (0 = no headache, 1 = mild headache, 2 = moderate headache, 3 = severe headache), functional disability for the day scale (0 = no disability: able to function normally; 1 = performance of daily activities mildly impaired: can still do everything but with difficulties; 2 = performance of daily activities moderately impaired: unable to do some things; 3 = performance of daily activities severely impaired: cannot do all or most things, bed rest may be necessary).

### Feasibility, acceptability, and participant satisfaction

Measures of feasibility include the ability to recruit the intended population from the SOD Headache Centre and Pharmacologic Clinic of the University Hospital Careggi of Florence, participant willingness to be randomized, and session attendance. In addition, the widely used Client Satisfaction Questionnaire-8 [40] is proposed. The credibility of treatment rationale and expectancy for improvement are evaluated via the Credibility Expectancy Questionnaire [41], which has been shown to be predictive of clinical outcomes in previous treatment trials and was adapted to include questions on expectancies regarding the likelihood of reduction of headache symptoms.

To maintain the blindness of the IEs, these acceptability and satisfaction measures will be administered at the end of the treatment period (session 8) by RAs not otherwise involved in the study.

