#### Data analysis plan

We will primarily focus on descriptive statistics to examine both feasibility, acceptability, and outcomes. This includes examining rates of study recruitment, participant’s willingness to be randomized, session attendance, and patient satisfaction. Additionally, we will compare rates of migraine attacks per month and their duration as well as the level of disability due to migraine and psychological measures. We will also examine the means of key variables (i.e., level of pain and disability caused by migraine, frequency, duration, and intensity of migraine attacks, anxiety, depression, psychological well-being, euthymia, distress) across baseline, session 4, session 8, and 3-month follow-up. We will use ANCOVA to compare means of variables [51], χ^2^ to compare frequencies, and a multivariate logistic regression analyses to identify independent predictors of psychological well-being among socio-demographic and psychological variables measured at baseline. The number of migraine attacks are recorded via the headache self-report daily diary following the rules suggested by Tfelt-Hansen et al. [36], namely (1) a migraine attack which is interrupted by sleep, or temporarily remits, and then recurs within 48 h is recorded as one attack; (2) an attack treated successfully with medication but with relapse within 48 h counts as one attack; and (3) a practical solution to differing these using diary entries over the previous month is to count as distinct attacks only those that are separated by an entire day headache free.

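### The named satisfaction questionnaire is fixed at session 8 with no stated collection from patients who stop earlier, so questionnaire satisfaction describes completers and is likely to be biased upwards

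*Protocol article*

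**What the plan says.** All references are to the protocol article.

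- **Aim.** The Background states that the pilot is to "evaluate the feasibility and acceptability of research procedures and interventions to investigate whether WBT improves outcomes relative to a control condition". The Study overview repeats feasibility and acceptability as purposes.
- **Instrument.** Under Feasibility, acceptability, and participant satisfaction, "the widely used Client Satisfaction Questionnaire-8 [40] is proposed". The Credibility Expectancy Questionnaire is named beside it.
- **Timing.** The same section says that "these acceptability and satisfaction measures will be administered at the end of the treatment period (session 8) by RAs not otherwise involved in the study". The reason given is to keep the independent evaluators blind. The Monitoring section agrees for credibility: "an assessment of treatment credibility will be provided at the end of session 8".
- **Second source.** The sections on well-being therapy and on the control condition each carry this sentence: "An assessment of treatment adherence, satisfaction, and side effects will be performed via ad hoc questions". Neither says when the questions are asked.
- **Use.** The Data analysis plan covers feasibility and acceptability by "examining rates of study recruitment, participant’s willingness to be randomized, session attendance, and patient satisfaction".
- **Drop-outs.** The Power calculation section provides for new enrolment until each group has 15 patients who complete the trial.

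**The concern.** A patient who leaves after session 2 or session 5 does not reach the point at which the questionnaire is scheduled. Attending session 8 depends partly on having found the treatment tolerable, and that is close to the property being measured. Averaging over those who attend therefore conditions satisfaction on something like acceptability itself.

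The clinical outcomes are less exposed. They are also taken after session 4, so a patient who leaves midway may still supply clinical data but no questionnaire satisfaction.

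Replacing drop-outs adds to the problem. An arm that loses many patients ends with the same 15 completers as an arm that keeps nearly everyone, and the replaced patients have no scheduled questionnaire. The two arms could then show similar satisfaction although one drove more patients away. The follow-on trial that the Discussion foresees would be planned on that figure. A later analysis plan cannot recover ratings that were never collected.

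**Working it through.** **The plan's own figure.** The only stated number that enters is 15 completers per group. A two-sample t test with two-sided alpha 0.05, power 0.95 and d = 1.38 needs 15 per group (power 0.954), and d = 2.76 needs 5 (power 0.967). Both agree with the article. The point does not depend on this calculation; 15 serves only as the number of completers.

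**Inputs not in the article (assumed).** The article gives no drop-out rate, no expected satisfaction and no definition of a satisfied patient. I take:
- p, the share stopping before session 8: 10%, 20% or 30%
- c, the share of completers who are satisfied: 80-90%
- s, the share of stoppers who would say they are satisfied: 0-50%

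**Size of the bias within an arm.**
- Share satisfied among all who started = c(1 - p) + s·p
- Share reported from session 8 data = c
- Overstatement = c - [c(1 - p) + s·p] = p(c - s)

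| p | Smallest (c = 0.80, s = 0.50) | Largest (c = 0.90, s = 0) |
|---|---|---|
| 10% | 0.10 × 0.30 = 3 points | 0.10 × 0.90 = 9 points |
| 20% | 0.20 × 0.30 = 6 points | 0.20 × 0.90 = 18 points |
| 30% | 0.30 × 0.30 = 9 points | 0.30 × 0.90 = 27 points |

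If satisfaction is analysed as a score, with completers 0.5-1.0 SD above stoppers, the overstatement is p × gap: from 0.10 × 0.5 = 0.05 SD to 0.30 × 1.0 = 0.30 SD. It is zero if p = 0 or c = s.

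**Difference between arms.** Take c = 0.90 and s = 0.40 in both arms, with 10% stopping in one and 30% in the other. Among all who started, satisfaction is 0.9 × 0.9 + 0.4 × 0.1 = 85% and 0.9 × 0.7 + 0.4 × 0.3 = 75%. Session 8 data give 90% in each, so a 10-point difference disappears.

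**How many patients are affected under the replacement rule.** Enrolment per arm for 15 completers is 15/(1 - p), rounded up:
- p = 10%: 15/0.9 = 16.7, so 17 enrolled and 2 without a questionnaire
- p = 20%: 15/0.8 = 18.75, so 19 enrolled and 4 without
- p = 30%: 15/0.7 = 21.4, so 22 enrolled and 7 without

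This assumes that all losses occur before session 8. Patients lost between session 8 and the 3-month follow-up would have been offered the questionnaire.

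**The case against.** A reader might infer that satisfaction as a whole is collected only at session 8, that patients who stop never contribute, and that acceptability is therefore overstated. The article does not support any of these.

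- **Only at session 8.** This is true of the named questionnaires. The ad hoc questions in both arms also cover satisfaction, and nothing ties them to session 8. Equally, nothing says that they are asked when a patient stops, so they are not a safeguard as written.
- **Never contribute.** Session attendance is measured and reported beside satisfaction, and adherence is assessed in both arms. An arm that loses more patients will show it there. What attendance cannot show is why: a patient who moved away and one who disliked the therapy look the same. The article also provides for recording missing data and clinical events. It does not promise reasons for stopping, but it does not establish that they would be lost.
- **Is overstated.** This is a likely direction, not a demonstrated result. Every rate above is assumed. The between-arm example also needs unequal drop-out, and this pilot could not measure it well. Ten points is 1.5 patients in 15, and at 85% against 75% the 95% half-width is 1.96 × √(0.85 × 0.15/15 + 0.75 × 0.25/15) ≈ 28 points.

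It can also be said that exit contacts are operational detail which a condensed article leaves to the full protocol. That would answer a complaint about silence. Here the article does state a time point, and following it as written leaves early stoppers out. The blinding reason explains who gives the questionnaire; it does not require that stoppers be left out.

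Finally, satisfaction is one of several descriptive items, and the article ties no test or progression threshold to it. This limits the consequence but does not remove the point.

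**Conclusion.** The point holds in a limited form. Questionnaire-based satisfaction, one part of the declared acceptability aim, is scheduled so that it describes patients who reach session 8, and replacement of drop-outs fills the final sample with completers. An upward bias is likely, larger in an arm that loses more patients. Its size cannot be derived from the article. Under the assumed ranges it is 3-27 percentage points, with about 2-7 patients per arm missing from the questionnaire data. There is no bias if nobody stops or if stoppers are as satisfied as completers.

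It does not follow that the acceptability evaluation as a whole is invalid, because attendance will be reported alongside and the ad hoc questions may reach some stoppers. This is an inexpensive improvement to a descriptive measure.

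**What to change.** 1. Amend the section on feasibility, acceptability and participant satisfaction. The same independent research assistants should give the questionnaire at session 8 or, for anyone who stops earlier, by telephone or post soon after the last attended session, with one question on the reason for stopping. Using the same staff keeps the evaluators blind.
2. State when the ad hoc satisfaction questions are asked in each arm, and set them so that early stoppers are covered.
3. Report satisfaction by arm for all randomised patients who started, including those later replaced. Show finishers and stoppers separately, beside session attendance and with the number who did not respond.

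The cost is one extra contact per early stopper, by staff already assigned to the task: about 2-7 per arm under the assumed drop-out. Some stoppers will not respond, so the bias is reduced and not removed, and the satisfaction figure will probably be slightly less favourable. The Trial status section says that recruitment has not started, so on the article's own account the change can be made before the first patient enters.
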